### Intervention

In the first step, the care programme offers a screening tool to detect symptoms of BPs, next to the usual (daily) observation and detection of BPs by nurses. When (symptoms of) BPs are detected, structured forms are used to analyse the behaviour in the next step of the care programme. The nursing staff starts the analysis, after which the elderly care physician and the psychologist continue analysis when necessary. The outcome of the analysis is discussed in pre-arranged multidisciplinary team meetings in which the members of the multidisciplinary team choose the treatment option (or options) they consider appropriate, resulting in a written treatment plan (third step). Psychosocial interventions are first line treatment options and psychotropics or physical restraints should only be used when psychosocial interventions have no or not enough effect. In the fourth step, treatment is evaluated. Standard scales are used for rating BPs when evaluating the effect of interventions. When treatment outcomes are unsatisfactory, alternative treatment options may be chosen and/or a new analysis will be done.

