### Sampling

We calculated the sample-size using the following assumptions: On average, a dementia SCU houses 20 residents. Based on a previous study, we expect that 5% of the residents' (legal) representatives will not give informed consent [1]. We expect no further attrition, because newly admitted residents will replace discharged and deceased residents during the study. For the primary outcome, we assume that our care programme leads to a 10 point decrease of BPs, measured with the Cohen-Mansfield Agitation Inventory (CMAI)[20]. Based on a Dutch study in NH patients [21], we assume a mean Intra Class Correlation Coefficient of 0.1. for clustering of BPs within a unit and a mean score of 47.7 (SD = 16.6) on the CMAI in NH patients with dementia.

Based on these assumptions and a significance level (alpha) of 0.05 and a power (beta) of 0.80, 14 dementia SCUs with 6 measurements are needed in a stepped wedge design.

The participating dementia SCUs will be recruited from NHs that collaborate with the VU University Medical Center (Amsterdam) and the Radboud University Nijmegen, Medical Center. The dementia SCUs participating in this study are not allowed to exchange staff between SCUs, in order to avoid carry-over effects, and thus dilution of the effect.

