### Data analysis

The CMAI-score and the NPI-NH score will be used as a primary outcome. Age, gender, length of stay, dementia severity, prescription of antipsychotics and of other psychotropics will be used as covariates. For the primary and secondary outcome analyses, multilevel linear regression and multilevel logistic regression analyses will be used. These analyses will calculate effects on neuropsychiatric symptoms, quality of life (Qualidem), prescription rate of antipsychotics, workload and job satisfaction of nursing staff and use of physical restraints.

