## Discussion

The aim of this study is to measure the effectiveness and cost-effectiveness of an evidence- and practice-based care programme for managing BPs in NH residents with dementia. Primary outcome is the effect on prevalence of BP. Secondary outcomes are the effect on quality of life, use of antipsychotics and physical restraints and on workload and job satisfaction of nursing staff. Additionally, an economic evaluation will be carried out.

We assume that implementation of the care programme will result in a decrease of BPs and, subsequently, in an increase of the quality of life of the residents. We also expect lower costs that will most likely be the result of a decrease of behavioural-problem related extra care, a decrease of medication, fewer admissions to hospital and also by a lower absence rate of nursing staff. Implementation is also expected to result in a lower workload and higher job satisfaction among nursing staff.

The chosen design to implement and evaluate the care programme is suitable for our purposes. Not only does the stepped wedge design increase the power of the study by enabling between-groups and within-group analyses, it also ensures that implementation of the care programme occurs in all participating care units, which likely increases motivation for participating in the study [40]. Except for the EQ5D, which is used to calculate QALYs, the chosen outcome parameters are all commonly used in the field of nursing home medicine and are also suitable for the population of severely demented patients [22,24,27,31].

The study has some limitations that should be mentioned. One limitation of the study is that, although data collection will be done by research assistants who are blinded for the trial condition, the NH staff will be aware of receiving the intervention, which may cause bias. To limit this bias, nursing staff will not be informed about the scores on the outcome measures. Another limitation is that we use proxy measures only, which may not be as reliable as patient measures [41]. However, in advancing stages of dementia, cognition and communication decrease, which makes the use of proxy measures inevitable [41]. Nevertheless, the described care programme for managing BP in NH residents with dementia and the chosen stepped wedge design seem very appropriate for our research goals.

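### Psychotropic prescription, which the programme aims to change, is a covariate with no limit to pre-programme values, so the primary models may miss the programme's total effect

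*Protocol article*

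**What the plan says.** The Data analysis section names the CMAI and NPI-NH scores as primary outcome and then gives the covariates: "Age, gender, length of stay, dementia severity, prescription of antipsychotics and of other psychotropics will be used as covariates". It does not say when the drug covariates are measured. The next sentence covers both outcome levels: "For the primary and secondary outcome analyses, multilevel linear regression and multilevel logistic regression analyses will be used". The effects to be calculated include "prescription rate of antipsychotics, workload and job satisfaction of nursing staff and use of physical restraints".

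Three other sections bear on the drug covariates:

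- **Intervention:** under the programme, "psychotropics or physical restraints should only be used when psychosocial interventions have no or not enough effect".
- **Discussion:** the authors expect savings from, among other things, "a decrease of medication, fewer admissions to hospital". They also write: "Secondary outcomes are the effect on quality of life, use of antipsychotics and physical restraints".
- **Sampling:** the cohort is open, since "newly admitted residents will replace discharged and deceased residents during the study".

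**The concern.** The aim is to evaluate the programme as a whole, so the target is its total effect on behaviour, including whatever comes about through changed prescribing. A covariate that the programme itself alters lies on the path from programme to outcome. Holding it fixed removes the part of the effect that runs through prescribing, whether that part helps or harms.

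There is a second problem. Prescribing and behaviour share causes, and prescribing responds to behaviour: the Background says antipsychotics are frequently used for behavioural problems. Conditioning on a variable that depends both on the programme and on such causes can create bias even if the drugs themselves have no effect on the CMAI.

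At stake is the primary effect estimate. If the adjusted estimate is carried into the economic evaluation, the cost per unit of behavioural improvement is affected too.

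**Working it through.** **1. Is the covariate on the causal path?** By the article's own account it is. The Intervention section restricts psychotropic use, and the Discussion predicts less medication.

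**2. Can the values be pre-programme?** For residents present before their unit's crossover, yes: all units are measured at T0, and all but the first group have further control cycles. For a replacement resident admitted after crossover, every value recorded on that unit is post-crossover, including the first. A baseline reading therefore covers only some residents.

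**3. Yardstick.** The article gives no figure for this adjustment. Its only calculated figure, the 14 units, does not enter the argument. Its Sampling inputs do give a standard error.

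- Inputs: SD 16.6, ICC 0.1, and 20 residents less 5% non-consent, so m = 19. The six cycles follow Table 1. Group sizes are 3, 3, 3, 3, 2, with the two-unit group assumed last.
- Between-unit variance: 0.1 × 16.6² = 27.56.
- Residual variance of a unit-cycle mean: 0.9 × 275.56 / 19 = 13.05.
- Generalised least squares with period effects and a random unit effect gives a standard error of **1.39** CMAI points.

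**4. Size of the shift.** In a linear model, adjusted effect = total effect + γ × d. Here d is the fall in the proportion using the drug, and γ is the coefficient of drug use in the adjusted model. If nothing else links prescribing and behaviour, γ is the drug's own effect b on the CMAI. With b = ±5 and d = 0.05 to 0.20, the shift is ±0.25 to ±1.0 points. If an unmeasured factor raises both prescribing and the CMAI, γ is pushed upwards.

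**5. Simulation.** Design as in step 3, with 200 replicates and unit and period fixed effects. Concurrent antipsychotic use was the only covariate. The total effect was set at -10, following the sample-size premise "we assume that our care programme leads to a 10 point decrease of BPs". Control use of 35%, d, b and the shared cause are assumptions; none is in the article. Entries are the adjusted minus the unadjusted estimate, in CMAI points.

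| Fall in use | b = -5 | b = 0 | b = +5 | b = -5, shared cause | b = 0, shared cause | b = +5, shared cause |
|---|---|---|---|---|---|---|
| 0 | +0.01 | +0.01 | -0.03 | 0.00 | +0.02 | +0.01 |
| 5 points | -0.23 | 0.00 | +0.23 | -0.09 | +0.16 | +0.41 |
| 10 points | -0.49 | 0.00 | +0.48 | -0.14 | +0.33 | +0.81 |
| 20 points | -1.00 | -0.02 | +0.99 | -0.25 | +0.73 | +1.74 |

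The extremes are an adjusted **-11.08** (unadjusted -10.08) and **-8.29** (unadjusted -10.03). In units of the standard error these shifts are 1.00 / 1.39 = 0.7 and 1.74 / 1.39 = 1.3. The unadjusted estimate stayed between -9.84 and -10.18 throughout, which is simulation noise around -10.

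**6. Prescribing that reacts to behaviour.** A separate simulation on the same design let the log-odds of prescribing rise by 0.8 per SD of CMAI, again an assumption.

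- True effect -10, and the programme also lowers prescribing directly by 0.6 on the log-odds scale: adjusted about -8.0.
- True effect -10, no direct effect on prescribing: adjusted about -9.0, because use falls as behaviour improves.
- True effect 0, programme lowers use by about 11 points: adjusted about +1.1.

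The range in step 5 is therefore an illustration and not a bound.

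**The case against.** **Timing.** The article does not say that concurrent values will be used, and a condensed article may leave covariate timing to the full protocol or analysis plan. A value fixed before the unit's crossover would be an ordinary baseline covariate. This stands, and it makes the bias conditional. It does not clear the rule, because residents admitted after crossover have no such value on their unit.

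**Size and sign.** Every prescribing input above is assumed, and the shift can go either way. A reader might infer that the adjustment necessarily hides benefit; the negative entries in the table show otherwise. Against the planned 10 points, the largest shift in the table is 1.74 / 10, about 17%, which would not stop an effect of that size from being detected. The simulations also omit the other planned covariates, and dementia severity could absorb part of the shared cause. All of this stands.

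**The antipsychotic model.** A reader might infer that this model is degenerate, with the outcome on both sides. That requires the full list to be applied literally to that model with same-cycle values, and the text does not clearly say so. The covariate sentence follows directly on the primary outcomes. The list also cannot apply unchanged to the nursing staff outcomes, which have no resident dementia severity or length of stay.

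**Secondary outcome status.** Only antipsychotic use is a secondary outcome. Other psychotropics are not, although the Intervention section restricts them equally.

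**Conclusion.** The point holds in conditional form. The article fixes two covariates that the programme is meant to change and does not confine them to pre-programme values. With concurrent or other post-crossover values, the CMAI and NPI-NH models would not estimate the total effect and could be biased through common causes of prescribing and behaviour.

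Under the stated assumptions the distortion runs from nothing to somewhat more than one standard error, in either direction. It is absent if prescribing stays the same or only pre-crossover values are used. The documents support neither a definite size or direction of bias nor the claim that the antipsychotic model must fail. The correction is still worth making before analysis, because the rule touches the primary estimate and costs almost nothing to change.

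**What to change.** Amend the covariate sentence in the Data analysis section as follows:

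- Remove prescription of antipsychotics and of other psychotropics from the main effectiveness models. Keep age, gender, length of stay and dementia severity.
- State that antipsychotic prescription is analysed only as an outcome, which also removes any doubt about its own model.
- If adjustment for drug use is wanted, confine it to a sensitivity analysis with values recorded before the unit's crossover. Keep post-crossover values for a separate mediation analysis, labelled as such.

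The downside is possibly a small loss of precision. Data collection and visits do not change.

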### Economic evaluation

The economic evaluation will be conducted from a societal perspective. We will measure and value all relevant costs, such as costs of the structured care programme, prescription of antipsychotics and hospital admission. Data will be collected using NH registries. Standardised case report forms will be used to measure the time invested by NH staff (e.g. recreational therapist, nursing staff, psychologist, elderly care physician) in both the intervention and the usual care condition. Absence rate of nurses will be retrieved from the participating NHs.

The EuroQol (EQ-5D) proxy version [37] will be used to measure quality adjusted life years (QALYS). Missing data on cost and outcomes will be imputed using multiple imputation according to the MICE algorithm [38].

A cost-effectiveness analysis will be conducted comparing the difference in total mean costs to the difference in effects on BPs; a cost-utility analysis will estimate the incremental costs per QALY. Bootstrapping will be used to estimate uncertainty of the incremental cost-effectiveness ratios (ICERs), which will be presented on cost-effectiveness planes. Cost-effectiveness acceptability curves and net monetary benefits will also be calculated [39]. Sensitivity analysis will include the most important cost-drivers.

## Discussion

The aim of this study is to measure the effectiveness and cost-effectiveness of an evidence- and practice-based care programme for managing BPs in NH residents with dementia. Primary outcome is the effect on prevalence of BP. Secondary outcomes are the effect on quality of life, use of antipsychotics and physical restraints and on workload and job satisfaction of nursing staff. Additionally, an economic evaluation will be carried out.

We assume that implementation of the care programme will result in a decrease of BPs and, subsequently, in an increase of the quality of life of the residents. We also expect lower costs that will most likely be the result of a decrease of behavioural-problem related extra care, a decrease of medication, fewer admissions to hospital and also by a lower absence rate of nursing staff. Implementation is also expected to result in a lower workload and higher job satisfaction among nursing staff.

The chosen design to implement and evaluate the care programme is suitable for our purposes. Not only does the stepped wedge design increase the power of the study by enabling between-groups and within-group analyses, it also ensures that implementation of the care programme occurs in all participating care units, which likely increases motivation for participating in the study [40]. Except for the EQ5D, which is used to calculate QALYs, the chosen outcome parameters are all commonly used in the field of nursing home medicine and are also suitable for the population of severely demented patients [22,24,27,31].

The study has some limitations that should be mentioned. One limitation of the study is that, although data collection will be done by research assistants who are blinded for the trial condition, the NH staff will be aware of receiving the intervention, which may cause bias. To limit this bias, nursing staff will not be informed about the scores on the outcome measures. Another limitation is that we use proxy measures only, which may not be as reliable as patient measures [41]. However, in advancing stages of dementia, cognition and communication decrease, which makes the use of proxy measures inevitable [41]. Nevertheless, the described care programme for managing BP in NH residents with dementia and the chosen stepped wedge design seem very appropriate for our research goals.
